### Activity monitor

Participants will also be asked to wear a GT3X ActiGraph accelerometer on the right hip for seven consecutive days (during waking hours) and complete a monitor wear diary. Activity monitors will be clearly numbered, charged and initialised for assessment. Each child opted in by their parents/carers will receive an activity monitor, an activity monitor diary and parental instructions. The activity monitor diary will ask participants to keep a record of the time they removed the belt, reason for removal and time they placed the belt back on. This will allow any water-based activities such as swimming to be captured. Participants will return their monitor and diary to school after 7 days following which study items will be collected by the research team before the data is downloaded and securely saved for processing.

### Follow-up

Twelve months after baseline data collection, both sets of data collection modes outlined above will be repeated as a follow-up assessment. Three weeks prior to this, schools will send a reminder to parents/guardians to make them aware of the remaining data collection in school. Processes described above for electronic survey and accelerometry data collection will be repeated in the following week.

### Withdrawal and loss to follow-up

Participants will be able to withdraw from the study up until publication of the results. Our default position if a participant withdraws from the study but does not request destruction of their data will be to retain data already collected; however, the participant will have the option to withdraw their data as outlined in the participant information sheets. The main trial information sheets will advise pupils, parents and carers on withdrawal procedures in relation to both the survey and accelerometer data; namely that the survey records data entered throughout and therefore pupils will need to specify to their teacher or parents/carers that they wish to withdraw their survey data, who will then inform the research team. Pupils will be advised to also tell their teacher or parents/carers if they wish to withdraw their activity monitor data, so that they can again inform the research team to organise withdrawal. Once a participant has withdrawn no further data will be collected from them.

### Process evaluation

In accordance with the Medical Research Council framework [27], the embedded process evaluation will explore intervention acceptability and the feasibility of implementing the intervention (including the extent to which the intervention was delivered as planned) and aim to understand mechanisms from the perspectives of participants and others and explore the context in which the intervention was conducted. Exploration of context will include the impact of the COVID-19 pandemic to separate out what is happening due to the context of COVID and what might be transferable to non-COVID times. The process evaluation will use both quantitative and qualitative measures as outlined below.

### Quantitative methods

At each intervention school the teacher overseeing intervention delivery will complete a weekly attendance register to record pupil attendance across sessions. The teacher will also complete a delivery logbook, using a standardised template, to assess whether community role models delivered the planned components (see Additional File 2) of each session fully, partially or not at all (i.e. fidelity scores). The focus on delivery of the components will be with regards the function of the components in line with the intervention theory, rather than specific form of delivery. A project team member will observe two randomly selected sessions in each school also completing the logbook template as a form of verification of teacher-assessed fidelity scores.

### Qualitative methods

At each intervention school, one-to-one interviews with teachers overseeing intervention delivery (1 per school), head teachers or member of the senior leadership team (1 per school), parents of participating girls (2 per school) and community role models (4 per school) will be conducted. Interviews will explore acceptability and feasibility of implementation of the intervention.

Three focus groups (involving 6 pupils in each) will be conducted at each intervention school with a sample of girls who have participated in the intervention and a separate group of year 5 boys. The focus group will be conducted at two-time points with the sample of girls, immediately post-intervention and 3 months later to explore experiences of the intervention, acceptability and barriers and facilitators to participation and longer term experiences of physical activity beyond intervention receipt. The focus group with boys aims to explore acceptability and potential unintended consequences of a targeted intervention for girls.

All peer role models will be invited to participate in a focus group at the end of intervention delivery to explore feasibility and acceptability of the peer role model component of the intervention and barriers and facilitators to involvement. We will also explore perceptions of ‘how’ the intervention is perceived to have worked or not and gather contextual considerations (e.g. COVID context and what’s specific to that, transferable beyond it).

### Adverse events

A risk assessment has found this trial to be low risk. All schools will be asked to notify the research team of any serious instance which is perceived to be study-related by submitting an anonymised version incidence report form. Any safeguarding issues arising during data collection will be reported immediately (and within 24 h of knowledge of the event) to the main school contact. The PI will continue to monitor reports and determine whether they are adverse events (AEs) or serious adverse events (SAEs). There are no expected adverse events related to the CHARMING Programme or research procedures.

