### Survey

The survey will be made available in English and Welsh and will be self-completed by pupils within the classroom under teacher supervision during school hours. Data collection will be facilitated by electronic data capture using a bespoke Qualtrics database, and paper copies of the survey will also be made available. Schools will be asked when signing up to the study if they would prefer electronic or pen and paper format. Each child opted into the study by their parents/carers will be allocated a unique Participant ID ahead of data collection, ensuring all participant data are pseudonymised.

The survey will collect data on demographics (age, gender and ethnicity), self-reported physical activity (Physical Activity Questionnaire for Older Children (PAQ-C scale)) [26], psychosocial outcomes (activity-based perceptions of autonomy, relatedness, competence and enjoyment), current after-school sport or physical activity club attendance (school and community) and health-related quality of life ((CHU-9D [21] and the EQ-5D-Y) [22]). Three schools will complete the EQ-5D-Y, and three schools the CHU-9D to reduce burden on pupils completing the questionnaires, whilst retaining the ability to answer feasibility questions. All questions will be closed response, with an ‘I do not want to answer’ option provided throughout. For electronic survey collections, the software will enable partial survey completions to be captured.

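### Schools are asked to report only serious events they perceive as study-related, yet the PI must sort reports into AEs and SAEs, so non-serious harms have no systematic route to the PI

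*Protocol article*

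**What the plan says.** All references are to the Protocol article. Under Adverse events, the reporting duty falls on both arms ("All schools will be asked to notify the research team"). What a school must do is "notify the research team of any serious instance which is perceived to be study-related by submitting an anonymised version incidence report form". Classification comes afterwards: "The PI will continue to monitor reports and determine whether they are adverse events (AEs) or serious adverse events (SAEs". Safeguarding has its own route: "Any safeguarding issues arising during data collection will be reported immediately (and within 24 h of knowledge of the event) to the main school contact". This section rates the trial as low risk and ends with "There are no expected adverse events related to the CHARMING Programme or research procedures".

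Five other sections bear on the point:

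- **Survey:** each child opted in by a parent is "allocated a unique Participant ID ahead of data collection, ensuring all participant data are pseudonymised".
- **Child recruitment and parental consent:** girls who are not in the study may still attend the programme.
- **Randomisation:** schools learn their allocation after baseline data collection.
- **Quantitative methods:** in each intervention school the overseeing teacher keeps a weekly attendance register, and "The teacher will also complete a delivery logbook, using a standardised template". A project team member observes two randomly chosen sessions per school with the same template.
- **Outcome measures, Progression criteria and Statistical analysis:** none of these mentions an adverse event count.

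**The concern.** The intake rule and the classification task do not fit together. To separate adverse events from serious ones, the PI needs reports of both kinds. Schools are asked for an event only after they have judged it serious and related to the study. A fall, a sprain or upset about wearing the belt would ordinarily fail the first test and would not be asked for.

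This is a stated rule and not a detail left out for brevity. It matters because the study is meant to inform whether and how a full-scale trial goes ahead, and the Discussion says that it will contribute evidence on unintended consequences. A handful of reports, or none, could be taken to confirm that no adverse events are to be expected, when the route was not set up to find minor ones.

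**Working it through.** The article states no adverse event rate, count or threshold, so there is no figure to reproduce. The check compares the stated rules and then asks what a count from this route could show.

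**1. Trigger against task.** Intake requires that the event is serious and that the school perceives it as study-related. The PI's task is to "determine whether they are adverse events (AEs) or serious adverse events (SAEs". No sentence in the section asks for events that fail either test. The safeguarding sentence does not fill the gap: it covers data collection only, sends the issue to the main school contact, and states no onward route to the PI.

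**2. Who judges, and when.** The school applies both tests before anything is sent. At baseline, staff do not yet know the allocation. During the programme and at 12 months they do, and in intervention schools the person best placed to report is likely to be the teacher overseeing delivery.

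**3. Other routes.** There are 4 intervention schools × 6 sessions = 24 sessions. Of these, 4 × 2 = 8 are observed, which leaves 16 without planned observation. The observer completes the fidelity template, which is not described as having a harms item. Interviews and focus groups may bring harms to light, but they involve a sample and are not described as adverse event collection.

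**4. What a low count could show.** Let r be the share of the 60 intervention girls (Sample size section) who have any harm. Let c be the share of those harms that a school judges both serious and related. Neither is in the article, so the values below are assumptions for illustration. Treating girls as independent:

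- expected reports = 60 × r × c
- P(no report) = (1 − r × c)^60

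| r | c | Girls harmed | Expected reports | P(no report) |
|---|---|---|---|---|
| 5% | 10% | 3 | 0.3 | 74% |
| 10% | 5% | 6 | 0.3 | 74% |
| 10% | 25% | 6 | 1.5 | 22% |
| 10% | 100% | 6 | 6.0 | 0.2% |

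The first two rows give the same result although twice as many girls are harmed in the second. The count depends only on the product r × c, so it cannot separate few harms from a strict filter. That conclusion needs no particular rate. The size of the shortfall does: over r = 5% to 30% and c = 2% to 25%, expected reports run from 0.06 to 4.5 and P(no report) from 94% to 1%.

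**5. The form.** Opted-in girls have a Participant ID and other attendees do not. If the form carries no identifier, the team may be unable to tell the two groups apart, recognise repeat events in one child, or relate an event to attendance or withdrawal. The Statistical analysis section plans to describe girls lost to follow-up by their engagement, so that link would be useful.

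**6. The expectation statement.** The Child assent section tells teachers to hand out monitors with care because of body-image issues. The plan thus foresees possible minor distress from a research procedure, which sits poorly with expecting no adverse events from such procedures.

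**The case against.** The strongest reply is proportionality. The programme is six one-hour after-school sessions in a trial assessed as low risk, and limiting reports to serious, related events is a defensible choice for such a study. The article is condensed, so definitions, forms and follow-up steps may well be in the full protocol. The trigger term is undefined and is not equated with a serious adverse event, and the fact that the PI may class a report as an ordinary adverse event implies that some non-serious reports could arrive. Observation, interviews and girls' focus groups at two time points may surface others, and the boys' group explicitly covers unintended consequences.

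Most of this stands as a limit on the point. Missing definitions are not held against the article, and it would be wrong to say that minor harms cannot reach the team. On anonymity, the article does not say that school, arm or date is removed, nor that the PI may not go back to the school. It also uses anonymised and pseudonymised loosely elsewhere. Linkage may therefore be hindered, but it is not shown to be impossible, and anonymity does not lower the count.

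The mismatch remains. Even under proportionate reporting, the printed trigger and the printed classification task describe different sets of events, and none of the other routes is systematic.

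**Conclusion.** The point holds as a mismatch between two stated rules. Non-serious harms have no systematic route to the PI, allocation-aware school staff make the first judgement of seriousness and cause after baseline, and a low count from this route would be weak evidence about minor harms. This rests on reading the trigger as printed and on the full protocol not setting a wider one.

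Its size cannot be given, because the article supplies no event rate. What can be stated is the exposure: at most 60 × 6 = 360 girl-sessions for study girls, plus any attended by girls outside the study.

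A reader might infer three stronger things that the document does not support:

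- **That minor harms never reach the PI, or that a near-zero count is built in.** The trigger term is undefined, other contacts exist, and the illustration runs from almost certain silence to almost certain reporting, depending on assumed inputs.
- **That counts must differ between arms by construction.** The trigger is relation to the study, not to the programme. Control girls also complete the survey and wear the monitor, and no between-arm comparison of harms is planned.
- **That a given number of events will be missed.** Any such number would rest wholly on an assumed rate.

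The matter does not affect the primary outcome or the progression criteria. It is worth correcting because the change is small and the study is meant to inform a larger trial.

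**What to change.** Reconcile the two sentences by widening intake and moving the judgement to the centre:

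- Schools report any injury, illness or distress that occurs during a programme session or is linked to the survey or monitor, whatever its perceived seriousness or cause.
- In intervention schools, add one yes/no incident line to the weekly delivery logbook. That logbook exists only in those schools, so add a simple equivalent at the baseline and 12-month data collection points in all six schools.
- Record the date and the Participant ID, or a non-study code for other attendees.
- Assign seriousness and relatedness centrally.
- Report counts descriptively. Give programme-session events per girl-session attended, using the attendance register, with the same children in numerator and denominator.
- Limit the statement that no adverse events are expected to serious events.

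The cost is one line on an existing form, a short item at two data collection points and a rewording of the rule. Teachers and the PI will handle a few more minor reports, and the event count will look less favourable.

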### Data analysis

#### Statistical analysis

The main outcomes in this feasibility trial are the rates of consent and recruitment (schools, peer-role models, year 5 girls), and retention at 12-month follow-up. Analysis of these data will be mainly descriptive (means and SD, median and 25th to 75th centiles for non-normal distributions, or *N* and %) as appropriate. Descriptive comparisons of these data will be made between intervention and control arms. Loss to follow-up in intervention and control groups will be reported. Demographic characteristics will be summarised descriptively as appropriate. We will characterise individuals that are lost to follow up at 12 months (with respect to demographics and intervention engagement.

For schools receiving the intervention, summary statistics will be presented for intervention reach and fidelity measures overall and by school/LA. This will include the proportion of recruited girls attending the first session, a minimum of one session and the number of session attendances per individual (max of 6). Mean (SD) or median (25th to 75th centiles) attendance per session will be calculated and summary statistics will be calculated on peer-role model engagement (e.g. attendance rates). Session attendance and presence or absence of the intervention components (role model delivering and participating in each session, question and answer opportunity with role models post-session, sign-posting) will be presented over time, overall and by school.

Accelerometry data will be analysed using a batch processing protocol; continuous periods of 60 min of zero counts will be considered as ‘non-wear time’ and removed. All data between 23:00 and 06:00 will be removed to ensure focus on awake time. Participants will be included in the analysis if they provide a minimum inclusion of 3 valid days. The percentage of original participants retained to 12-month follow-up who provide valid useable accelerometry data will be reported. Average counts per minute (CPM) will be used as a measure of total physical activity. Using the Evenson cut-points [28], the average daily minutes spent sedentary (cut-point of < 100 CPM), in MVPA (≥ 2296 CPM) and time-segment-specific time spent in each activity intensity (e.g. during club, after school or at weekends will be estimated using 7-day accelerometer data and summarised overall and by trial arm. Mixed-effects linear regression will be used to estimate direction of intervention effects on accelerometer-measured physical activity on the adjusted mean difference between intervention and control groups, alongside a 95% confidence interval (CI). School-level variance will be accounted for by inclusion of school as a random effect, and any remaining differences in the baseline assessment of the outcome measure, and local authority area (by which the randomisation was stratified), as fixed factors. The school-level intra-class correlation (ICC) coefficient for average daily minutes of MVPA over the 7 days will be estimated alongside a 95% CI. Whilst likely non-significant due to limited power, this should be in the direction of a favourable intervention effect.

Response rates and level of completion of the survey measures such as (self-reported physical activity (PAQ-C scale), psychosocial outcomes (activity-based perceptions of autonomy, relatedness, competence and enjoyment) and current after-school sport or physical activity club attendance (school and community), at baseline and 12-month follow-up will be reported using descriptive statistics. Regression models will also be used to estimate direction of intervention effects on 12-month survey outcomes. Mixed-effect models will take the clustering of individuals in schools into account using a random model and adjust for baseline outcomes.

All analyses will be intention to treat (i.e. students will be analysed in the groups in which their school was randomised to, regardless of adherence to the intervention) and missing outcome data will not be replaced. The analysis and reporting of this cluster randomised controlled trial will be in accordance with CONSORT (Consolidated Standards of Reporting Trials) guidelines {Eldridge, 2016 #354}.

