#### Sample size

As this study is focused on feasibility, the purpose is to provide estimates of key parameters for a future full-scale trial, rather than to power the current study to detect statistically significant differences. A total of 90 children within 6 recruited primary schools (allowing for an average of 15 girls in year 5) will allow an estimation of feasibility criteria with reasonable precision across a diverse range of context (e.g. intervention fidelity, completion of assessments, and valid primary outcome data). For girls within the intervention schools only (*n*=60), we will estimate that 50% will attend the intervention (i.e. minimum of one session) within ±12.7 percentage points using a 95% confidence interval. Similarly, for girls from all schools (*n*=90), the parameter of 70% returning valid primary outcome data can be estimated within ±9.5%, and 80% will complete baseline/follow-up to within ±8.3%.

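### As written, the baseline-adjusted models would by default leave out girls with a valid 12-month outcome but no valid baseline, at a modest cost in precision

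*Protocol article*

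**What the plan says.** Three statements in the protocol's Statistical analysis section bear on this.

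- The mixed-effects model for accelerometer-measured activity has school as a random effect and includes "any remaining differences in the baseline assessment of the outcome measure, and local authority area (by which the randomisation was stratified), as fixed factors".
- For the survey outcomes, "Mixed-effect models will take the clustering of individuals in schools into account using a random model and adjust for baseline outcomes".
- For all analyses, "missing outcome data will not be replaced". The same sentence defines intention to treat: "students will be analysed in the groups in which their school was randomised to, regardless of adherence to the intervention".

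The section also sets a wear rule: "Participants will be included in the analysis if they provide a minimum inclusion of 3 valid days". It does not say at which wave the three days are needed. No sentence says how a girl with a 12-month value but no usable baseline enters a model.

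The Randomisation section says that schools learn their arm only after baseline data are collected, and that staff and participants are blinded at that stage.

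**The concern.** There is one follow-up wave, so the response is the 12-month value and the baseline value is a covariate. A regression omits any record with an empty covariate unless the plan says otherwise. The protocol itself describes the baseline values as outcomes, so its no-replacement sentence is naturally read as covering them too.

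Such girls are foreseeable. The Child recruitment section lets a child do the survey, the accelerometer or both, and a week of wear can fail the validity rule at one wave and pass at the other. Their 12-month outcomes would be collected and then not used in the adjusted models. With six schools and about 90 girls, that widens an interval that is already wide.

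The loss is also avoidable. Baseline is recorded before anyone in the schools knows the allocation, so whether it is missing cannot be a response to a known arm.

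**Working it through.** **Inputs.** From Sample size: "A total of 90 children within 6 recruited primary schools (allowing for an average of 15 girls in year 5"), and 70% with valid primary outcome data. From Randomisation: a 2:1 ratio, so four schools against two. From the fifth progression criterion: a target of 70% valid at both waves. The protocol gives no overlap of validity between waves, no intraclass correlation (ICC) and no baseline to follow-up correlation (r). These are assumed below, with ICC from 0 to 0.10 and r from 0.3 to 0.7.

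**Step 1: the plan's own figure.** The plan says "the parameter of 70% returning valid primary outcome data can be estimated within ±9.5" percentage points. The half-width is 1.96 × √(0.70 × 0.30 / 90) = 1.96 × 0.0483 = 0.0947, or 9.5 points. It reproduces as a simple binomial interval. The plan gives no corresponding figure for girls valid at follow-up only.

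**Step 2: girls lost.** The number lost is the number valid at 12 months minus the number valid at both waves.

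| Assumption | Valid at 12 months | Valid at both (in model) | Lost |
|---|---|---|---|
| A. 70% valid at both; waves equal and independent (√0.70 = 0.837 each) | 0.837 × 90 = 75.3 | 63 | 12.3 (16% of 75.3) |
| B. 70% valid at each wave; independent | 63 | 0.49 × 90 = 44.1 | 18.9 |
| C. 70% at each wave; same girls fail both times | 63 | 63 | 0 |
| D. 70% at each wave; least possible overlap | 63 | 63 − 27 = 36 | 27 |

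**Step 3: approximate effect on the standard error.** Take outcome variance 1, with m₁ girls per school valid at both waves and m₂ valid at follow-up only. Then

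SE² = (1/4 + 1/2) × [ICC + 1/(m₁/((1 − ICC)(1 − r²)) + m₂/(1 − ICC))].

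Example for A with ICC 0.05 and r 0.5: m₁ = 63/6 = 10.5 and m₂ = 12.3/6 = 2.05.

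- Without the follow-up-only girls: √(0.75 × (0.05 + 1/14.74)) = 0.297.
- With them: √(0.75 × (0.05 + 1/16.90)) = 0.286, a reduction of 3.7%.

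Over the assumed ranges the reduction is 1.4 to 7.9% for A, 3.5 to 15.2% for B and 6.2 to 22.9% for D. For C it is zero. The top of each range needs ICC = 0 and r = 0.3. The formula lets follow-up-only girls have their own, larger residual variance, which an ordinary model does not, so it can be somewhat optimistic.

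**Step 4: simulation of A.** Six schools of 15, ICC 0.05, no true effect, about 84% valid at each wave, 3,000 runs. The complete-case model was compared with a pooled-mean fill plus missing-baseline indicator. Both used known variance components and no local authority term.

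| r | Baseline missingness | SD of estimate, complete case | SD, fill plus indicator | Reduction |
|---|---|---|---|---|
| 0.3 | at random | 0.317 | 0.301 | 5.0% |
| 0.5 | at random | 0.304 | 0.296 | 2.6% |
| 0.7 | at random | 0.271 | 0.268 | 1.1% |
| 0.3 | depends on baseline activity | 0.327 | 0.308 | 5.8% |
| 0.5 | depends on baseline activity | 0.296 | 0.284 | 4.1% |
| 0.7 | depends on baseline activity | 0.273 | 0.272 | 0.4% |

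The mean error was at most 0.013 SD for either method in every row. Neither analysis showed material bias.

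**The case against.** The strongest reply is that the protocol does not state the rule at issue. Its sentence concerns missing outcome data, and read narrowly it leaves the baseline covariate open. A separate statistical analysis plan is mentioned and not shown, and it may settle the matter. This stands in part: omission is a consequence of the text, not a declared exclusion. But because the text itself labels the baseline values as outcomes, that plan would have to narrow the protocol's sentence in order to keep these girls.

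Other replies also carry weight.

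- The counts borrow a validity rate from the fifth progression criterion, which requires more than three days including a weekend day. The analysis rule asks only for three valid days, so the real loss may be smaller.
- Poor wear probably recurs in the same girls, which moves the loss towards scenario C.
- The main outcomes are recruitment and retention rates, the models are meant to show direction only, and the Progression criteria section disclaims any indication of effectiveness.
- Assent is taken at the data-collection session, so a girl absent at baseline may never have joined the trial. The point is therefore confined to girls recruited at baseline.

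A reader might infer something stronger: that the intention-to-treat label is contradicted, or that restricting the model to better compliers biases the comparison. The documents support neither. Intention to treat is defined only by allocated group, and a complete-case model by allocated group meets that definition. The simulation found no material bias, even with missingness that depended on baseline activity.

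**Conclusion.** The point holds as a minor one. Followed as written, the adjusted accelerometer and survey models would by default omit recruited girls with a valid 12-month outcome and no valid baseline. What is lost is precision in the adjusted difference and its interval.

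The illustrative loss is about 12 of 90 under scenario A, and 0 to 27 if validity is 70% at each wave. The simulated gain from keeping the girls under A is about 1 to 5% in the spread of the estimate with missingness at random. Larger gains in the formula need less overlap between waves. All of this rests on assumed overlap, ICC and correlation, and the number of schools limits what can be gained.

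Descriptive summaries and completion rates need not lose these girls. The same is true of an ICC from an unadjusted model, and the protocol does not say which model its ICC comes from.

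**What to change.** Reword the missing-data sentence so that non-replacement applies to 12-month outcomes only. Then state, for accelerometer and survey models alike:

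- every girl recruited at baseline who has a valid 12-month outcome is analysed in her school's allocated arm;
- a missing baseline covariate is set to the pooled baseline mean, the same value in both arms, with a missing-baseline indicator in the model;
- the analysis restricted to girls valid at both waves is reported as a sensitivity analysis.

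This costs a sentence or two, one degree of freedom for the indicator and one further analysis. Girls with a filled baseline get no true baseline adjustment, so each adds somewhat less information than a girl measured twice. A joint model of baseline and follow-up would be an acceptable alternative. Neither approach addresses missing 12-month outcomes, which stay unreplaced as the protocol intends.
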